## Abstract

**Background:**

Reducing sedentary behavior and increasing physical activity in people with type 2 diabetes (T2D) are associated with various positive health benefits. Just-in-time adaptive interventions offer the potential to target both of these behaviors through more contextually aware, tailored, and personalized support. We have developed a just-in-time adaptive intervention to promote sitting less and moving more in people with T2D.

**Objective:**

This paper presents the study protocol for a microrandomized trial to investigate whether motivational messages are effective in reducing time spent sitting in people with T2D and to determine what behavior change techniques are effective and in which context (eg, location, etc).

**Methods:**

We will use a 6-week microrandomized trial design. A total of 22 adults with T2D will be recruited. The intervention aims to reduce sitting time and increase time spent standing and walking and comprises a mobile app (iMove), a bespoke activity sensor called Sedentary Behavior Detector (SORD), a messaging system, and a secured database. Depending on the randomization sequence, participants will potentially receive motivational messages 5 times a day.

**Results:**

Recruitment was initiated in October 2022. As of now, 6 participants (2 female and 4 male) have consented and enrolled in the study. Their baseline measurements have been completed, and they have started using iMove. The mean age of 6 participants is 56.8 years, and they were diagnosed with T2D for 9.4 years on average.

**Conclusions:**

This study will inform the optimization of digital behavior change interventions to support people with T2D Sit Less and Move More to increase daily physical activity. This study will generate new evidence about the immediate effectiveness of sedentary behavior interventions, their active ingredients, and associated factors.

**Trial Registration:**

Australian New Zealand Clinical Trial Registry ACTRN12622000426785; https://anzctr.org.au/Trial/Registration/TrialReview.aspx?id=383664

**International Registered Report Identifier (IRRID):**

DERR1-10.2196/41502

## Introduction

### Overview

People with type 2 diabetes (T2D) have higher levels of sedentary behavior (SB) and lower levels of moderate to vigorous intensity physical activity (PA) compared with those without T2D [1]. Device-based measurement of SB has shown that people with T2D spend >64% of their daily waking time sedentary [1], which has subsequently sparked calls for targeted behavior change programs to reduce SB in this population, in addition to the promotion of regular PA [2].

SB has become a distinct target for individuals who are susceptible to or have been diagnosed with T2D [3]. It is suggested that people with T2D break up their sitting time by light PA, which can serve as a means for gradually adopting a more active lifestyle [4]. Reducing sitting time by either standing or light ambulation has been shown to improve glucose homeostasis among people at risk of or diagnosed with T2D [3].

Ubiquitous mobile health (mHealth) technologies such as smartphones and wearable sensors offer considerable potential to improve access to and delivery of behavior change support for reducing SB and promoting PA [5,6]. Progress in mHealth technology has enabled the design of just-in-time adaptive interventions (JITAIs), which aim to deliver behavior change support in real or near time, matched to when users need or want the support [7,8]. JITAIs harness information captured through mHealth technologies (smartphone sensors, GPS, and internet access) to determine which behavior change support component should be delivered and tailor it to an individual’s changing context (where) or status (when) [9]. The delivery of more contextually aware intervention support at more salient times to end users is hypothesized to enhance behavior change compared with other delivery approaches (eg, face-to-face and websites) [9].

It has been argued that conventional experimental designs are not sufficient to support the development of JITAIs because they do not enable researchers to determine empirically when a particular intervention component should be delivered and whether a JITAI that was delivered exerted the intended effect [10]. Traditional randomized controlled trial designs evaluate the overall effect of an intervention on a specific behavior or health outcome, not specific components of that intervention. Moreover, randomized controlled trials do not provide information on the particular time when the intervention had an effect and the moderators that affected the behavior change [11].

Other study designs, such as factorial designs, enable researchers to determine the effects of each intervention component, the interactions between components, and the dosing of the intervention. However, they are unable to delineate the time when the intervention was most receptive and what moderators influenced the intervention [11]. To address these limitations, Klasnja et al [11] proposed the microrandomized trial (MRT), which, they argued, could supplement the use of behavioral theory to guide the development of JITAIs. The MRT design provides data on the effects of specific intervention components, changes in effects over time, and potential moderators, including contextual and psychological factors [11]. Due to the dynamic nature of SB and PA that change throughout the day and in various contexts, adaptive designs such as MRT align well with interventions targeting SB and PA behavior change [12]. The MRT design has been suggested as necessary to leverage the potential of smartphones as a tool to improve PA and reduce SB [13]. MRT enables assessing the immediate effects of antisedentary and walking interventions [14] and therefore contributes to the optimization of SB and PA interventions.

Microrandomization refers to randomly allocating an intervention option at relevant times when a person would be most responsive to an intervention (based on theory, the person’s past behavior, and the current context), thereby enhancing the effectiveness of the intervention [11]. MRTs explain the causal relationship between each randomized intervention component (eg, Sit Less or Move More notifications) and the proximal effects (ie, what happens in a limited time window, eg, within 1 hour, following the randomized intervention component) [11]. The distal outcome results from an aggregation of proximal effects obtained through repeated exposure to intervention components over time [11]. For example, a distal outcome would be people achieving recommended levels of PA and longer-term clinical outcomes such as improved glycemic control or improved fasting or postprandial glucose [15].

### Aims

The primary aim of this study is to assess the effectiveness of theory-based motivational messages for reducing proximal sitting time and increasing proximal standing or walking time (ie, nonsitting time). The secondary aims involve (1) assessing what type of behavioral components (ie, behavior change techniques) are most effective in reducing sitting time and increasing standing and walking time, measured proximally, and (2) determining relevant contextual moderators for reducing sitting time and increasing standing and walking time.

## Methods

### Design

A 6-week MRT will be conducted (see Figure 1). Using this design, participants will be randomly assigned an intervention option (Sit Less message, Move More message, or no intervention) at each relevant decision point.

**Figure 1 figure1:**
[figure not shown]
A summary of the microrandomized trial (MRT) design. Target group, availability conditions, study duration and arms, randomization probability, and outcomes are presented. BCT: behavior change technique; T2D: type 2 diabetes.

### Participants and Recruitment

#### Overview

Participants will be recruited digitally through social media advertisements (eg, Facebook and Instagram). Moreover, posters will be placed on noticeboards of general practitioner and specialist clinics, and emails will be sent to potential participants who have indicated their willingness to participate in research studies. The plain “language statement and consent form” will be sent to eligible participants who express their interest in participating before any data collection.

#### Sample Size

A total of 22 participants are estimated to detect a small proximal treatment effect size of 0.13 for increasing nonsitting time with 80% power at the level of 5% statistical significance. This was based on the assumptions of 5 decision points per day, a constant randomization probability of 0.7, and an expected participant availability of 70% [16].

### Eligibility Criteria

Eligible participants will be adults with T2D, aged between 35 and 65 years, who own an Android smartphone (version 7.0 or higher) and currently interact or engage with apps, have no limitations (including physical problems and medical complications) to engage in low- and moderate-intensity PA, are able to communicate in English, and can provide informed consent.

Volunteers who use other activity trackers and mobile apps that target PA, highly active people, those diagnosed with T2D less than 3 months ago, and people with psychiatric problems, attention, or memory issues will be excluded. We assume highly active people as those who meet World Health Organization (WHO) recommendation of 10,000 steps per day or 150 minutes of moderate to vigorous PA per week. The International Physical Activity Questionnaire—Short Form will be used to assess activity levels [17]. A 1-week run-in period will assess nonadherence with the activity tracker. Individuals with more than 50% incomplete data will be excluded.

### Intervention Platform

The intervention comprises a bespoke mobile app (iMove app) [18] and a Bluetooth-enabled wearable sensor (SORD) developed and validated by our research group [19]. iMove is a JITAI that aims to support people to decrease sedentary time (Sit Less) and increase PA (Move More) [20]. It consists of a home tab that illustrates sitting, standing, and walking activities, an activity tab to select activities manually in situations where technical issues exist with the app, a goal setting tab to set sitting and walking goals, a notification history tab to compile previous notification messages, and a profile tab (see Figures 2 and 3). SORD is a bespoke thigh-worn device that connects to the iMove app and measures sitting, standing, lying, and PA (eg, walking) [19].

**Figure 2 figure2:**
[figure not shown]
iMove app images.

**Figure 3 figure3:**
[figure not shown]
Sedentary Behavior Detector (SORD) device.

### Intervention

#### Overview

Through the iMove app, participants will receive a series of Sit Less and Move More intervention messages (notifications) to serve as cues to action [21] and increase readiness to engage in activity. A pop-up message will appear on the phone screen with a sound effect when a notification is received. There will be 2 intervention options, which include Sit Less (sedentary interruption and transition to standing) and Move More (walking) for 1.5-3 minutes, approximately equivalent to 500-1000 steps, and a control option (no messages). Participants can switch off the push notification for a certain amount of time on any given day.

A list of messages is provided in Multimedia Appendix 1.

Notifications are adapted to 4 different context dimensions, including time of day, day of the week (weekend vs weekdays), location (home vs workplace), and weather conditions (good or suitable for PA, rainy and cold or not suitable for PA). Notifications are delivered on 5 occasions (decision points) throughout the day and include morning, lunchtime, afternoon 1, afternoon 2, and evening (details are presented in the “Decision Points” section below).

At each decision point, participants are randomized only if they are available (ie, they are not driving, not sleeping, not active already, and are connected to the internet). The following probabilities are used for randomization: 70% in the intervention (35% SB, 35% PA) and 30% as active control at each particular decision point. GPS will assist with the recognition of driving if the user is on the move. A preset time (9 PM to 8 AM) will be considered for rest and sleeping. In addition, both driving and sleeping can be manually modified by users.

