### Data Analysis

#### Primary Analysis

Data from the 22 participants who generated 42 days of expected data, totaling 4620 decision points, will be analyzed. The study days will be continued until we reach the required number of days of data for each individual. Moreover, to deal with missing data at various decision points that could result from Bluetooth issues with the transfer of data or any other reasons (eg, activity states not being recorded), we will impute 0 for all missing minutes of sitting, standing, and walking.

MRT data will be analyzed using the weighted and centered least-squares estimator as previously described [27]. Using this analytical method, time-varying covariates can be handled, and the causal effect can be consistently estimated. Statistical analyses will be performed using R software (R Foundation for Statistical Computing) using the geepack R package.

Primary outcome measures include decision point, day, availability, interventions, and proximal change in activity states (ie, within 1 hour after the intervention is delivered). Overall effects of delivering a suggestion compared with not providing a suggestion on the subsequent 1-hour sitting, standing, and walking behaviors will be assessed. Moreover, linear treatment effects for Sit Less and Move More suggestions will evaluate the interaction between suggestion effects (ie, Sit Less or Move More) and decision points.

Statistics including β estimate, 95% CI, and *P* values will be reported for the average proximal effect as well as the multivariate effect (main effect). Sit less, Move More, and no suggestion (ie, control) conditions will be compared.

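### Switched-off notifications are not among the availability conditions, so muted participants are still randomised to messages whose cue they do not receive, which dilutes the proximal effect and costs power

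*Protocol article*

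**What the plan says.** All references are to the protocol article.

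- **Intervention, Overview.** Messages are cues to action, shown as a pop-up with a sound. The same section adds: "Participants can switch off the push notification for a certain amount of time on any given day".
- **Same section, availability.** The rule for each occasion reads: "participants are randomized only if they are available (ie, they are not driving, not sleeping, not active already, and are connected to the internet". This list is introduced as a definition, not as examples, and notification status is not on it. Available participants are allocated 70% to a message (35% of each type) and 30% to control. Of the listed states, two can be set by hand: "both driving and sleeping can be manually modified by users". Muting is not linked to either.
- **Sample Size.** The section states: "A total of 22 participants are estimated to detect a small proximal treatment effect size of 0.13". The target for that effect is given as "with 80% power at the level of 5% statistical significance". The inputs are 5 decision points per day, a randomisation probability of 0.7 and 70% availability. The section does not say whether the 70% allows for muted time.
- **Proximal Outcome and Primary Analysis.** The outcome hour starts at sending in the first section and at delivery in the second. The primary contrast is worded "Overall effects of delivering a suggestion compared with not providing a suggestion".

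**The concern.** In a microrandomised trial the availability rule does two jobs: it decides which decision points are randomised, and it defines the times to which the primary effect applies. Here the rule leaves out a state that the same section lets participants create at will. During muted periods a message assignment and a control assignment differ very little, because the timed cue is off in both. Such points enter the primary contrast while contributing little or no effect.

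At stake is power. The trial has 22 participants and was sized at 80% for a small effect, so there is little margin. The text also does not say how a muted decision point is to be coded, which leaves the meaning of the primary effect open for those points.

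**Working it through.** **Inputs from the article.** N = 22; 42 days × 5 = 210 decision points per person; availability τ = 0.7; randomisation probability ρ = 0.7; standardised effect d = 0.13; α = 0.05.

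**Assumed input.** s, the share of available points that are muted, is not in the article; 5%, 10% and 20% are used. The message is taken to have no effect within the hour when muted.

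**Step 1: reproduce the planned sample size.** The usual power calculation for this design is a noncentral F test with noncentrality

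λ = N × 210 × τ × ρ(1−ρ) × d² = 22 × 210 × 0.7 × 0.21 × 0.0169 = 11.48.

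- 2-df test (linear effect model with a flat true effect; denominator df 22 − 2 − 2 = 18): power 0.802, required N = 22. This matches the plan.
- 1-df test (constant effect; denominator df 22 − 1 − 1 = 20): power 0.896, required N = 18.
- A quadratic model with no initial effect and its peak at day 21 also gives N = 22 (power 0.819).

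The article does not state the shape of the effect over time, so both the 2-df and 1-df results are carried forward.

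**Step 2: as written, analysed by assignment.** The effect becomes 0.13(1−s), so λ = 11.48(1−s)².

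**Step 3: muted points treated as unavailable.** The effect stays at 0.13 and availability becomes 0.7(1−s), so λ = 11.48(1−s).

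| s | Effect as written | λ as written | Power as written, 2 df / 1 df | λ if unavailable | Power if unavailable, 2 df / 1 df |
|---|---|---|---|---|---|
| 0 | 0.130 | 11.48 | 0.80 / 0.90 | 11.48 | 0.80 / 0.90 |
| 5% | 0.124 | 10.36 | 0.76 / 0.86 | 10.90 | 0.78 / 0.88 |
| 10% | 0.117 | 9.30 | 0.71 / 0.83 | 10.33 | 0.76 / 0.86 |
| 20% | 0.104 | 7.35 | 0.60 / 0.73 | 9.18 | 0.70 / 0.82 |

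On the 2-df model, restoring 80% power as written would need 24, 27 or 33 participants at s = 5%, 10% or 20%. With muted points unavailable it would need 23, 24 or 27.

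**Step 4: why the coding should be stated.** Suppose points were coded by whether a message was delivered. All muted points would then fall in the no-message group and make up s/(0.3 + 0.7s) of it: 0.10/0.37 = 27% at s = 10%, and 0.20/0.44 = 45% at s = 20%. If the outcome at muted points differed by an assumed 0.2 SD, the estimate would shift by 0.2 × 0.27 = 0.054 or 0.2 × 0.455 = 0.091. The sign depends on whether people mute when they sit more or when they sit less.

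**The case against.** **Bias is not shown.** A reader might infer from the word delivering in the Primary Analysis section that muted points will be counted as control and the primary contrast biased. The article does not support that. The Design section randomises to Sit Less message, Move More message or no intervention; the outcome hour is anchored to sending under Proximal Outcome; the estimator is weighted and centered least squares; and no text recodes points by receipt. Delivery coding is permitted by loose wording but not adopted. This objection stands.

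**Dilution is not an error of inference.** By assignment, the estimate is a valid effect of assigning a message in an app that users can mute. This also stands: the cost is power and a smaller effect, not an invalid test.

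**The gain depends on an unknown rate.** At 5% muting the fix recovers only about 2 power points. At 10% it recovers about 5 (2 df) or 4 (1 df), and on the 1-df reading power remains above 80% even without it. Only at 20% is the gain about 10 points (2 df) or 9 (1 df). This is fair, and it limits the size of the point.

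**Other stronger readings.** It would go too far to say that muted participants cannot see the message: the app has a notification history tab, so what is lost is the timed pop-up and sound. Nor does the article suggest that driving or sleep status is edited after a message; availability is settled before randomisation.

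**The source is condensed.** Figure 1 is captioned as presenting availability conditions and is not shown, and the app may already handle muting. That is possible, but the written rule is a closed list and omits it.

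**Conclusion.** The point holds as an inconsistency between a permitted feature and the stated availability rule. As written, muted participants are randomised and the proximal effect is diluted to 0.13(1−s). On the 2-df model that reproduces the planned 22 participants, the loss at N = 22 is about 4, 9 and 20 power points for assumed muted shares of 5%, 10% and 20%; treating muted points as unavailable cuts it to about 2, 5 and 10. These figures assume no message effect during muted hours and an s that the article does not give. The test itself remains valid under analysis by assignment, and no bias is established. This is a change worth making, not a fatal flaw.

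**What to change.** 1. Add notifications being switched on to the availability conditions, checked and recorded immediately before randomisation.
2. State that every available decision point is analysed by its randomised assignment, and reword the primary contrast so that it cannot be taken as coding by delivery.
3. In the Sample Size section, state whether the 70% availability includes muted time.
4. The article reports 6 participants already enrolled. Reclassify their muted points as unavailable only if mute status before randomisation was recorded; otherwise keep those points as randomised.

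**Cost.** One more condition in the app's availability check and a few sentences of text. Realised availability falls slightly, and the estimated effect then applies to unmuted times only, which should be said when results are reported.

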#### Decision Points

A total of 5 decision points, from 8 AM to 8:30 PM, will be selected as shown in Table 1.

**Table 1 table1:** Occasions (decision points) when notifications are delivered.

Decision point	Time
Morning	8 AM to 10:30 AM
Lunchtime	10:30 AM to 1 PM
Afternoon 1	1 PM to 3:30 PM
Afternoon 2	3:30 PM to 6 PM
Evening	6 PM to 8:30 PM

#### Intervention Messages

Notifications were developed by the research team and incorporate effective behavior change techniques to Sit Less and Move More. Behavior change techniques including behavior substitution [22], social support [23], problem-solving or barrier identification [23], instruction on how to perform the behavior [22,24], providing information on the consequences of PA specific to the individual [23], prompts or cues [24], prompting generalization of a target behavior [23], goal setting [23], self-monitoring [22], and feedback on behavior [22] were used to create messages. Table 2 presents examples of intervention messages and their associated behavior change techniques.

**Table 2 table2:** Examples of Sit Less and Move More messages and their respective behavior change techniques.

Message type and behavior change technique			Example message
**Sit Less**			
	Behavior substitution	You have been sitting for about 1 hour this morning. Why not stand up and do some stretches for 2-3 minutes.	
	Social support	Ask your partner to do some house chores with you (e.g., sweeping, mopping, vacuuming, etc.). It is more fun when you do this together while talking as well!	
	Problem-solving or barrier identification	You might not notice your long periods of sitting time, but it adds up to a lot of hours (e.g. we may sit during meals, travelling to/from work, in front of the computer, watching TV,…). Now it’s the right time to take a break and stand up and do some stretches or warm-up exercise.	
	Instructions on how to perform the behavior	Time to stand up: you may want to grab a drink of water, talk on the phone while walking around or go and talk to your colleagues instead of emailing them.	
	Providing information on the consequences of physical activity (PA) specific to the individual	It’s important to spend less time being sedentary. You’ll have more balance, as well as stronger muscles and bones. Now it’s a good time for a 10 minutes walk around the house.	
	Prompts or cues	Why not go take one of your favorite books and enjoy reading! This way you break up your sitting.	
	Prompting generalization of a target behavior	It looks like you are doing well reducing your sitting time during the mornings. Try to break your sitting time in the evenings as well. It’s the time!	
	Goal setting	Your daily sedentary behaviour goal is *[<VALUE hours]*. While working, you can stand up and do some stretches. This helps you achieve your daily goal.	
	Self-monitoring	Check how much time you spent in sedentary (sitting) state yesterday.	
	Feedback on behavior	Congratulations! You achieved your daily sedentary behaviour goal *[<VALUE hours]* today. Keep it up!	
